## Abstract

**Background:**

Return to work after gynaecological surgery takes much longer than expected, irrespective of the level of invasiveness. In order to empower patients in recovery and return to work, a multidisciplinary care program consisting of an e-health intervention and integrated care management including participatory workplace intervention was developed.

**Methods/Design:**

We designed a randomized controlled trial to assess the effect of the multidisciplinary care program on full sustainable return to work in patients after gynaecological surgery, compared to usual clinical care. Two hundred twelve women (18-65 years old) undergoing hysterectomy and/or laparoscopic adnexal surgery on benign indication in one of the 7 participating (university) hospitals in the Netherlands are expected to take part in this study at baseline. The primary outcome measure is sick leave duration until full sustainable return to work and is measured by a monthly calendar of sickness absence during 26 weeks after surgery. Secondary outcome measures are the effect of the care program on general recovery, quality of life, pain intensity and complications, and are assessed using questionnaires at baseline, 2, 6, 12 and 26 weeks after surgery.

**Discussion:**

The discrepancy between expected physical recovery and actual return to work after gynaecological surgery contributes to the relevance of this study. There is strong evidence that long periods of sick leave can result in work disability, poorer general health and increased risk of mental health problems. We expect that this multidisciplinary care program will improve peri-operative care, contribute to a faster return to work of patients after gynaecological surgery and, as a consequence, will reduce societal costs considerably.

**Trial registration:**

Netherlands Trial Register (NTR): NTR2087

## Background

### Health care problem

Research on duration of full recovery and Return To Work (RTW) after (laparoscopic) gynaecological surgery has shown large discrepancy between expected physical recovery and actual return to work [1-3]. This may be explained by the fact that duration of recovery and RTW is mainly influenced by the expectations of the patient and employer, rather than by physical factors or the type of surgery [4-6]. However, in most cases there is hardly attention for RTW expectations [7]. In general, gynaecologists do discuss the needs and risks concerning the surgical intervention and expected duration of hospitalization with their patient, but structural convalescence recommendations regarding the resumption of (work) activities are mostly not provided [1,8]. In addition, after discharge the patient usually has only one post-operative check-up six weeks after surgery, which is focused on examination of the physical condition. Other medical care is fragmented and given only on demand, as a result of which patients often do not know whom to contact for support in case of postoperative complaints. Due to Dutch legislation, patients with paid work who do not RTW within six weeks after surgery, are generally consulted by their Occupational Physician (OP). However, as a result of the lack of recognised guidelines on the resumption of (work) activities and poor communication between the gynaecologists, General Practitioners (GPs) and OPs, often indistinct and conflicting recommendations are given and additionally most physicians do not differentiate according to the type of surgery [9-11]. These factors contribute to uncertainties and irrational beliefs of patients, which may result in delayed recovery, prolonged sick leave and reduced quality of life [12,13].

The Dutch Health Council stated, in line with the International Classification of Functioning, disability and health (ICF) model that there is a strong need for multidisciplinary recommendations for resumption of postoperative work activities [14,15]. However, little is known about patients' needs, (illness) beliefs and preferences regarding postoperative care and resumption of work activities [16]. Therefore, we previously explored patients' peri-operative needs using focus group discussions with gynaecological patients and performing a systematic review of the literature [17]. Detailed multidisciplinary convalescence recommendations were developed in collaboration with the medical board of gynaecologists, OPs and GPs through a modified Delphi consensus method with experts [18]. To mirror the target group, the focus group discussions and Delphi study were geared towards patients who underwent a hysterectomy (abdominal, vaginal, laparoscopic) or laparoscopic adnexal surgery on benign indication. These types of surgeries were chosen, because they are the most frequently performed (major) gynaecological surgical procedures with a considerable postoperative effect on recovery and RTW and yearly count for more than 17.500 procedures in the Netherlands [19].

### Multidisciplinary care program

Based on the results of the modified Delphi study, the outcomes of the focus group discussions, the literature review and considering both the ICF model as well as the Attitude, Social influence and self-Efficacy (ASE) model in which important determinants of recovery and RTW are described [20,21], a multidisciplinary care program for gynaecological patients undergoing surgery was developed. The care program aims at the different aspects of curative treatment as well as at personal and external factors. In addition, it tries to encourage patients in resuming activities and participation in the society. The program consists of an interactive e-health intervention, integrated care management and a participatory workplace intervention. The e-health intervention was developed through an intervention mapping protocol [22] and specifically aims at the empowerment of gynaecological patients and their environment during the pre- and postoperative period (from around four weeks before until eight weeks after surgery) [17]. This includes encouragement of patients in resuming daily and work activities. If the patient is still on sick leave 10 weeks after surgery, the integrated care management and participatory workplace intervention will be offered. This part of the intervention is based on a previous study with patients with chronic low back pain [23], and was adapted to our target group for this study.

### Objectives

The main objective of this study is to evaluate the effectiveness of the multidisciplinary care program (e-health intervention, integrated care management & participatory workplace intervention) compared to usual care regarding full sustainable RTW for patients after hysterectomy or laparoscopic adnexal surgery on benign indication. Secondary objectives of the study are 1) to study the effect of the multidisciplinary care program on general recovery, quality of life, pain intensity and complications; 2) to investigate how the program is evaluated by the patients, their health care providers and their employers and 3) to validate the multidisciplinary convalescence recommendations developed in het Delphi study [18].

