### Intervention group; multidisciplinary peri-operative care program

Patients in the intervention group, receive normal usual peri-operative care with the adjustment that the care providers supply standardized detailed convalescence recommendations to the patients [18]. In addition, this group will get access to an e-health intervention and, when they have not returned to work completely within ten weeks after surgery, supplementary care of a clinical occupational physician and (if relevant) a workplace intervention by an Occupational Therapist (OT) will be offered. This stepped care approach of additional care will be described in detail below.

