#### Step 1: all patients get access to an e-health intervention from four weeks before surgery

To improve peri-operative gynaecological care, an interactive e-health intervention aiming at the empowerment of gynaecological patients during the peri-operative period including return to normal activities and work was developed [17]. This e-health intervention targets at behaviours of patients as well as of gynaecologists, GPs, OPs, employers and family members. It provides tools to compose detailed tailored instructions on the resumption of (work) activities, based on the operation date and how the surgery went (input of gynaecologist). These recommendations are based on a Delphi study among gynaecologists, GPs and OPs, using a structural consensus method including a systematic review of available literature [18]. The e-health intervention additionally provides tools (e.g. a video) to improve the communication between patients, care-providers and employers, to prevent conflicting recommendations and stimulate patients and employers to discuss potential RTW problems and to develop a work reintegration plan. Furthermore, general information on the surgical procedure itself, the (possible) consequences of the surgery and clear instructions about which symptoms require additional consultation of care providers or adaptation of convalescence recommendations, is available by the e-health intervention. In addition, it supplies an extensive list of frequently asked questions and a forum to contact other patients. Finally, patients' recovery can closely be monitored by the website, allowing the e-health intervention to advise the patient to contact a clinical occupational physician for support with reintegration when she has not RTW ten weeks after surgery. Table 1 presents an overview of the various tools of this e-health intervention.

**Table 1 T1:** Structure of the e-health intervention [17]

Tool	Content	Involved stakeholders
1. Compose a work reintegration plan	■ Tool to compose a detailed reintegration plan with adaptations for work if necessary.	➢ Patient, Employer, OP
2. Resume normal activities	■ Tool to compose detailed advice about when normal (private) activities can be carried out again	➢ Patient, family
3. Evaluate complications	■ Estimate severity and consequences of a complication	➢ Patient, gynaecologist
4. Recovery Monitor	■ Monitoring recovery and offering assistance when relevant	➢ Patient

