### Outcome Measures

#### Data-collection

The follow-up period will be 26 weeks after surgery (baseline). All the outcome variables are measured using self-report online questionnaires [35] and will be taken at baseline, 2, 6, 12 and 26 weeks after surgery. In general, the longer the recall period, the less accurate individuals are in reporting for example the use of health care services. Although no evidence on the optimal period is provided by literature, 12 and 26 weeks are frequently used and generally accepted [36]. Little agreement exists on the accuracy and validity of self-reported health care utilization and absenteeism data [37]. However, regarding sickness absence general consistency in the self-reporting can be relied on when recall is required within one month [37,38]. Therefore, in this study a monthly self-reported calendar of sickness absence per post was chosen to measure RTW. Furthermore, gynaecologists will complete questionnaires one day after surgery of each patient and at the end of the study. Employers will be asked to evaluate the e-health intervention eight weeks after the surgery of their employee. When patients, gynaecologists and employers do not fill out the questionnaires within one week, they will receive a reminder per email. If no response follows, they will be reminded by a telephone conversation. In addition to the questionnaires and calendars, the e-health intervention used by the intervention group will measure the use of the intervention, complications and (satisfaction with) recovery. Table 3 presents an overview of the outcomes and variables measured in this study.

**Table 3 T3:** Overview of outcome measures & variables in this study

Outcome measures & variables	T_0_ Baseline^d^	T_1_ 2 wks after surgery	T_2_ 6 wks after surgery	T_3_ 12 wks after surgery	T_4_ 26 wks after surgery
Primary					

1) Return to work^a^		measured monthly^e^			

Secondary					

2) Total duration of sick leave^a^		measured monthly^e^			

3) First RTW^a^		measured monthly^e^			

4) Recovery					

• Recovery specific QoL (RI-10)	X	X	X	X	X

• Performed activities			X		

• Performed activities measured by e-health intervention^b, c^		at least 2, 4, 7, 14, 21, 28, 42, 56, 84 days after surgery			

5) Functional and general health status (SF36, EuroQoL)	X			X	X

6) Pain intensity (Von Korff)			X	X	X

7) Empowerment (GSES)		X	X	X	

8) Health care usage (TicP)				X	X

9) Occurrence of complications during the post-operative period			X	X	X

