#### Secondary Outcome measures

2) The total duration of sick leave (due to the consequences of the surgery) during the 26 weeks follow-up period; measured by a monthly calendar of sickness absence.

3) First RTW; measured by a monthly calendar of sickness absence.

4) Recovery; measured by a validated Recovery Specific Quality Of Life questionnaire RS-QOL(RI10) [40], an extended list of (graded) activities based on the detailed convalescence recommendations given to the patients of the intervention group [18] and a recovery monitor which is a tool of the e-health intervention of the intervention group.

5) Functional and general health status (Quality of life); assessed according to the standard Dutch version of the EuroQol [41] and the Short-form health survey (SF-36) [42,43].

6) Pain intensity; measured using Von Korff questionnaire [44].

7) Empowerment; assessed by the Dutch adaptation of the General Self-Efficacy Scale [45].

8) Health care usage; measured by the Tic-P questionnaire [46] and valued according to the prices in the guidelines for economic evaluation in the Netherlands [47].

9) The occurrence of complications in the post-operative period; assessed by questions based on the complication registration form of The Dutch Society of Obstetrics and Gynaecology (NVOG) [48]. Patients in the intervention group do also answer these questions more frequently through a tool of the e-health intervention, in order to register possible side effects of the intervention and to determine and inform them when symptoms require additional consultation of care providers or adaptation of convalescence recommendations.

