### Strengths and limitations

The implementation of this study in six general (teaching) and a University hospital is a good reflection of the Dutch health care situation. In addition, the selection bias of patients will be restricted through the proactive way of inviting all patients on the waiting lists to participate in the RCT. Therefore, selection will take place only based on clearly defined in- and exclusion criteria. A third strength is the blinding of the patients, which will minimize the Hawthorne and placebo effect [56]. Furthermore, the primary outcome measure in this study is full sustainable RTW, which takes into account recurrences of sick leave within four weeks after RTW and therefore reduces underestimation of work-loss days [57]. Another strength regarding the outcome measures is the evaluation of patients' health and recovery through clinical, participatory and activity outcome measures. By doing so, the influence of the care program on the different aspects of human functioning and state of health according to the ICF model, will be evaluated [14]. All patients receive their own research code according to which all data were stored in the databases. This ensures blinded analysis of the data by the researchers. Finally, this is the first study to extensively evaluate consensus-based guidelines with detailed convalescence recommendations regarding return to normal and work activities after gynaecological surgery [18,58]. The guidelines represent a consensus opinion of expert-based knowledge between gynaecologists, GPs and OPs and this study will show whether these recommendations reflect realistic recovery times for gynaecological patients and will bring about a quicker recovery without an increase in complications compared with usual care.

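### Objective 3: serial data on graded non-work activities come only from the arm that is told the recommended times, and the list common to both arms is given once, at six weeks

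*Protocol article*

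**What the plan says.** The Objectives section of the protocol article lists, as the third secondary objective, "to validate the multidisciplinary convalescence recommendations developed in het Delphi study". The Strengths and limitations section indicates what this is to deliver: "this study will show whether these recommendations reflect realistic recovery times for gynaecological patients and will bring about a quicker recovery without an increase". The increase meant is one of complications, relative to usual care. The quoted sentence contains two separate claims. One is that the recommended times are realistic. The other is that giving them speeds recovery safely.

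Women in the intervention arm receive the times under test. The section on the intervention group says that "the care providers supply standardized detailed convalescence recommendations to the patients". Step 1 says of the website: "It provides tools to compose detailed tailored instructions on the resumption of (work) activities". Controls receive usual care and a placebo website with a standard leaflet.

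Under Secondary Outcome measures, item 4 (recovery) includes "an extended list of (graded) activities based on the detailed convalescence recommendations given to the patients of the intervention group". In Table 3 the row "Performed activities" is marked once, under T2 (6 weeks), with no restriction by arm. The next row, activities recorded through the website, is scheduled for at least days 2, 4, 7, 14, 21, 28, 42, 56 and 84, and a footnote restricts it to the intervention arm.

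**The concern.** Testing whether a recommended time is realistic means comparing it with when women actually resume the activity. In the intervention arm the women have been told the time and encouraged to act on it, so observed agreement mixes two things: the advice was realistic, or the advice was followed. The control arm is the only group not given these times, apart from the contamination that the article itself discusses. For graded non-work activities it is observed once, at week 6. An activity that a control resumes later is recorded only as not yet resumed.

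At stake is the realism half of objective 3. The Policy implications section foresees broad implementation of the guidelines. If intervention-arm agreement were then read as evidence that the times are right, the support would be weaker than it looks for any activity commonly resumed after six weeks.

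**Working it through.** The plan gives no figure for objective 3 to reproduce. The sample size (191, or 212 with 10% dropout) is for the primary outcome and plays no part here. The check is a count from Table 3 and its footnotes.

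**Scheduled readings of graded activities**
- Week 6 is day 6 × 7 = 42, and week 12 is day 12 × 7 = 84.
- Control arm: one list, at day 42. Readings after day 42: 0.
- Intervention arm: the same list at day 42, plus the website monitor at days 2, 4, 7, 14, 21, 28, 42, 56 and 84, which is at least 9 entries. Entries after day 42: days 56 and 84, so 2.

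**What the week-6 list can show in controls**

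The article does not say whether the list asks current status or the date of resumption.
- If it asks dates, resumption up to day 42 can be placed against a recommended time. Later resumption cannot.
- If it asks status, only the proportion resumed by day 42 is known. Where fewer than half have resumed, the control median lies beyond day 42, which is later than any recommended time at or before day 42. How much later stays unknown.
- Under either form, where the recommended time lies after day 42, the list shows which controls resumed before week 6. It cannot show whether the others resumed before, at or after the recommended time.

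**What is observed in both arms after week 6**
- Work: the monthly sick-leave calendar, from surgery to 26 weeks, gives first return, full sustainable return and total sick leave.
- RI-10: weeks 2, 6, 12 and 26.
- Complications: weeks 6, 12 and 26.

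The gap is therefore confined to dating non-work activities in controls after week 6. The RI-10 does not fill it, because a quality-of-life score gives no resumption time for a particular activity.

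**Size**

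The recommended times are in a cited source and not in the article, so the share of activities resumed after day 42 cannot be calculated. For scale only: with about 191 / 2 ≈ 95 evaluable controls, each 10% who have not resumed a given activity by week 6 is about 0.10 × 95 ≈ 10 women with no resumption time. The monitor entries at days 56 and 84 suggest that some later resumption was expected.

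**The case against.** The strongest reply is that much of objective 3 is well served. The recommendations cover work, and controls' return to work is followed monthly for the whole 26 weeks. The second claim in the Discussion, faster recovery with no more complications, is a randomised comparison, and the Policy implications section makes that claim the condition for implementation. Compliance with the recommendations is asked separately in the process evaluation, so adherence need not be silently taken for realism. Nothing in the article says that intervention-arm agreement will be presented as validation, and the analysis for objective 3 may be set out in the full protocol.

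Most of this stands, and it limits the point. A reader might infer that resumption after week 6 is never seen in controls, or that the whole validation is circular. The calendar rules out the first, and the randomised comparison rules out the second. A reader might also take "Return to work after gynaecological surgery takes much longer than expected, irrespective of the level of invasiveness", or the ten-week trigger for step 2, as proof that many activities are resumed late. Both concern work, which is the outcome that is observed.

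It would also be wrong to treat control timing as the natural standard. The Health care problem section says that recovery depends mainly on expectations and that usual advice is often unclear or conflicting. Control timing is thus itself shaped by advice, and it is the delay that the programme sets out to shorten.

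What the reply does not remove is the schedule itself. The time points in Table 3 are stated, not left to another document. Compliance questions describe adherence, but they cannot tell a woman who resumed on the advised day because she was told to from one who would have done so anyway.

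**Conclusion.** The point holds in a limited form. For graded non-work activities, serial measurement is confined to the arm given the recommended times. Controls have one reading against at least ten in the intervention arm (1 list + 9 monitor entries), and none against two after week 6. The claim that the trial will show whether the recommended times are realistic is thus weakly supported for activities resumed after six weeks.

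How many activities that covers is unknown. The conclusion assumes only that some are resumed after week 6, which the monitor's own schedule suggests. It concerns part of one secondary objective. The primary outcome, the sample size and the randomised comparisons are untouched. The change is a worthwhile low-cost improvement and does not correct an error in the main analysis.

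**What to change.** Repeat the activity list in both arms within the existing 12-week (T3) questionnaire. For each activity not yet resumed at week 6, ask the date of first resumption. This extends control observation from day 42 to day 84, the last scheduled monitor entry.

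Report resumption times against the recommended times in both arms, by type of surgery. Present the control arm as a comparison under usual advice and not as a gold standard. Describe intervention-arm agreement as reflecting adherence as well as realism. Qualify the sentence in Strengths and limitations to match. If the questionnaire can no longer be changed, qualify that sentence anyway, saying that for non-work activities resumed after week 6 the only scheduled serial data come from women who were given the times.

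The cost is a few items in a questionnaire that both arms already receive, and recall of dates over about six weeks (12 − 6). That is longer than the one month the article regards as dependable for sick-leave recall, so the dates will carry some error. Added contamination should be small, because controls already see the list at week 6. Activities resumed after week 12 would remain undated.
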